#### Digital Trail Making Test

Executive functioning will be assessed using a self-reported online version of the dTMT, which includes TMT-A and TMT-B. In TMT-A, participants are required to connect a sequence of numbers in order. In TMT-B, participants must alternately connect numbers enclosed in circles and squares, following the sequence while ensuring that the pen remains in contact with the paper throughout the process. Participants’ executive functioning will be evaluated based on the time taken to complete the entire test and the accuracy of the number connections [40].

In this study, the dTMT will be used to assess medical students’ executive functioning. The TMTs are widely used in neuropsychological assessments due to their sensitivity to various neurological disorders. The test consists of 2 conditions (A and B) [41]. In part A, medical students will be instructed to draw a line sequentially connecting a total of 26 numbered circles as quickly as possible. In part B, each student will be asked to connect a series of 26 circles containing either a number or a letter, alternating between them. Both conditions will be scored based on the total time taken to complete the tasks and the frequency of errors made.

#### Other Sleep Measures

Average sleep parameters, including SOL, TST, NOA, WASO, SQ, and SE (calculated as TST/time in bed × 100), will be derived using the PSQI [42]. Inclusion criteria will be assessed using the baseline sleep diary. Participants will be instructed to document information about their SOL, WASO, NOA, early morning awakenings, number of nocturnal awakenings, TST, and SE for 10 days before the intervention (out of the previous 14 consecutive days) [43].

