### Research Aim and Hypotheses

This study aims to elucidate the effects of improved SQ on executive function. The following hypotheses will be investigated in the trial:

ICBT-I will lead to a significant improvement in SQ compared with the SHE intervention at 1 month (T2), 3 months (T3), and 6 months (T4) postintervention.ICBT-I will lead to a significant improvement in executive functioning compared with the SHE intervention at 1 month (T2), 3 months (T3), and 6 months (T4) postintervention.ICBT-I will lead to a significant improvement in total sleep time (TST), SOL, number of awakenings (NOA), wake time after sleep onset (WASO), and sleep efficiency (SE) compared with the SHE intervention at 1 month (T2), 3 months (T3), and 6 months (T4) postintervention.Dysfunctional beliefs, attitudes about sleep, presleep worry, and sleep hygiene will significantly mediate the between-group differences in study outcomes at 1 month (T2), 3 months (T3), and 6 months (T4) postintervention.

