#### The Pittsburgh Sleep Quality Index

The Pittsburgh Sleep Quality Index (PSQI) is an instrument used to assess sleep over the previous month, and it is completed at the beginning of 2 study periods. This validated tool, based on polysomnographic research, consists of 19 self-reported items that evaluate 7 components: subjective SQ, sleep duration, sleep disturbance, sleep latency, habitual SE, use of sleeping medications, and issues related to sleep dysfunction. The instrument provides an index score ranging from 0 to 21 points. Scores greater than 5 indicate significant sleep problems, while lower scores reflect high or acceptable SQ [39].

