### Data Analysis

Data will be analyzed using SPSS version 29 (IBM Corp.). Descriptive statistics will be used to obtain information on dropout rates, recruitment, and completeness. All participants will be included in the intention-to-treat analysis for assessing the main efficacy of the intervention, with no planned interim analysis for efficacy or futility. The baseline characteristics of participants will be presented according to their randomized group, with no inferential statistical tests performed at this stage.

For the RCT design, outcome measures will be assessed for normality and presented as either means with SD or medians with IQR, depending on the data distribution. Participants’ characteristics will be summarized using descriptive statistics, with categorical data presented as frequencies and percentages, and continuous data presented as means (SD) or medians (IQR). Normality will be tested using the Kolmogorov-Smirnov and Shapiro-Wilk tests.

Changes in all outcome measures (ie, SOL, TST, NOA, WASO, SQ, SE, dysfunctional beliefs about sleep, presleep arousal, and SHI) from pretreatment (T0) to the first (T1), second (T2), and third (T3) time points will be assessed for treatment effects using repeated measures analysis of variance. Both treatment and time interaction effects will be examined. Paired samples *t* tests will then be conducted within each condition to evaluate possible simple or main effects. Significant findings and statistical trends will be further analyzed using Cohen *d* effect size, which accounts for the correlation between pre- and posttreatment values.

Potential confounding factors, particularly class year and gender, will be addressed and analyzed as variables that may influence the research outcomes. These factors will be incorporated into the analysis through both univariate and multivariate linear regression analyses, allowing for the isolation of each factor and its association with the outcomes of interest.

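### Number of awakenings and wake time after sleep onset cannot be computed from the PSQI, the source the protocol names for them, so 2 of the 5 hypothesis 3 parameters have no usable stated source at T2 to T4

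*Protocol article*

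**What the plan says.** The protocol article, under Other Sleep Measures, names one source for all the sleep parameters: "Average sleep parameters, including SOL, TST, NOA, WASO, SQ, and SE (calculated as TST/time in bed × 100), will be derived using the PSQI".

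The section on the Pittsburgh Sleep Quality Index says that its 19 items "evaluate 7 components: subjective SQ, sleep duration, sleep disturbance, sleep latency, habitual SE, use of sleeping medications, and issues related to sleep dysfunction". On its output it says: "The instrument provides an index score ranging from 0 to 21 points".

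Hypothesis 3, under Research Aim and Hypotheses, claims superiority of internet CBT-I on "total sleep time (TST), SOL, number of awakenings (NOA), wake time after sleep onset (WASO), and sleep efficiency (SE) compared with the SHE intervention", at T2 (1 month), T3 (3 months) and T4 (6 months). The Data Analysis section puts the same parameters into the repeated measures analysis of variance: "Changes in all outcome measures (ie, SOL, TST, NOA, WASO, SQ, SE, dysfunctional beliefs about sleep, presleep arousal, and SHI".

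Other Sleep Measures also describes a sleep diary that covers both awakenings and WASO. It is introduced as the baseline diary for checking inclusion criteria, and participants are told to record "TST, and SE for 10 days before the intervention (out of the previous 14 consecutive days".

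**The concern.** The protocol assigns NOA and WASO to an instrument that, as the protocol describes it, reports neither. The instrument that does record them is scheduled only before treatment. If this stays as it is, whoever analyses the trial must choose after data collection between dropping two prespecified outcomes, improvising a proxy from a PSQI item that does not fit, and borrowing values from some other record. Any of these would be a data-dependent change to a stated hypothesis.

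The timing also matters. The Results section reports T1 and T2 assessments complete for everyone enrolled by 20 June 2024, with T3 and T4 due by July 2025. A diary not kept at a past visit cannot be recovered.

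**Working it through.** No formula or published figure is involved. The check sets each hypothesis 3 parameter against the PSQI components that the protocol lists, then looks for any other follow-up source.

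**Step 1. Parameters against PSQI components**

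| Hypothesis 3 parameter | Matching component in the protocol's list |
|---|---|
| TST | sleep duration |
| SOL | sleep latency |
| SE | habitual sleep efficiency |
| NOA | none |
| WASO | none |

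The nearest entry for the last two is sleep disturbance. The protocol does not describe it as a count of awakenings or as a time awake.

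**Step 2. Other possible sources at T2 to T4**

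- *Baseline diary (Other Sleep Measures).* Records both NOA and WASO, but only before the intervention and for eligibility.
- *Programme diary (The Internet Group, CBT-I).* Lists night awakenings but not WASO, and is part of the treatment, not an outcome assessment.
- *Diary in the sleep hygiene arm (The Internet-Based SHE).* Daily entries are recommended within the modules. Their content is not given.
- *Outcome assessment (Outcome Measures, Overview).* An online set of 56 items including the Trail Making Test, taking 20 to 30 minutes. A diary kept over several days does not fit that description.
- *Enrolment battery (Data Collection Procedures).* PSQI, Trail Making Test, DBAS-16, PSAS and SHI, with no diary.
- *Follow-up (Monitoring of Intervention and Follow-Up Assessment).* The list of what is reassessed includes SE but neither NOA nor WASO.

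None of these places clearly schedules a measurement of NOA and WASO at T2, T3 or T4.

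**Step 3. Size**

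- Parameter-by-time comparisons in hypothesis 3: 5 parameters × 3 visits = 15.
- Comparisons on NOA and WASO: 2 × 3 = 6.
- Share without a usable stated source: 6 of 15, or 2 of 5 parameters.

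**Step 4. What can still be collected**

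- Enrolled by June 2024: 48 + 49 = 97, all with T1 and T2 done.
- Still to enrol against the target: 120 − 97 = 23.

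If no diary was kept at T2, NOA and WASO at T2 could come from at most those 23 participants. On the reported timetable, T3 and T4 remained open.

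**The case against.** The best defence is that the follow-up section says the instruments set out earlier will be used again, and the diary is among the things set out earlier. On that reading NOA and WASO would exist at T2 to T4. This reading is possible but loose: Other Sleep Measures ties the diary to the pre-intervention period and names the PSQI as the source. Even if it is right, the sentence naming the PSQI is wrong and needs correcting.

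A second defence is that the protocol names seven components, not the wording of all 19 items, and cites a reference for the derivation. That is fair as far as it goes. The documents show that no listed component gives either quantity; they do not show what every item asks. Nothing in the protocol, however, explains how a count or a duration would be obtained.

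Nor is this detail that an article may leave to a fuller document. The article states a source, and its own description of that source does not support it.

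Three stronger readings are tempting, and the documents do not support them:

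- *Part of hypothesis 3 is untestable outright.* It is untestable from the named source. A repeated diary would make it testable.
- *The rest of hypothesis 3 merely restates the primary outcome.* SOL, TST and SE overlap with three of the seven components, so they are weak corroboration of the PSQI total. But they can be analysed in their own units (SE is defined as a percentage), which is not the same as the 0 to 21 index.
- *The trial will compare diary baselines with PSQI follow-ups.* Nothing in the protocol says so. It is a trap to avoid, not a demonstrated defect.

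**Conclusion.** Wrong as written. The protocol names the PSQI as the source of NOA and WASO, the PSQI as it describes it provides neither, and the diary that records both is specified only before the intervention. Two of five hypothesis 3 parameters, 6 of 15 comparisons at T2 to T4, cannot be computed from the stated source.

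The reach is limited. SOL, TST and SE are unaffected, the sleep parameters are secondary outcomes, and the primary outcomes, sample size and randomisation are untouched.

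The conclusion rests on taking the protocol's list of PSQI components as complete for this purpose, and on reading the diary as a pre-intervention instrument, as its description says. The count of 15 uses the visits in hypothesis 3.

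**What to change.** Before analysis, as a dated change:

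1. Correct Other Sleep Measures so that NOA and WASO come from the same sleep diary used at baseline, collected identically in both arms at the assessments still to come.
2. Remove NOA and WASO from hypothesis 3 and from the Data Analysis list at any visit where no such diary data exist. If none exist after baseline, remove both outcomes altogether.
3. Keep SOL, TST and SE on the PSQI at all visits. T1 and T2 are already collected for the 97 enrolled, and switching midway would itself mix instruments.
4. State that diary values will not be paired with PSQI values to measure change.

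The diary kept during treatment is not a substitute. The programme version lists no WASO, entries in the sleep hygiene arm are only recommended, and T1 is not a hypothesis 3 time point.

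The cost is a short online diary at the remaining visits, a small burden on participants, or the loss of two secondary endpoints.

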#### Dysfunctional Beliefs and Attitudes About Sleep-16

The DBAS-16 contains 16 items designed to measure sleep-related beliefs and attitudes [44]. A 10-point Likert scale is used to rate the items, ranging from 1=strongly disagree to 10=strongly agree. The minimum and maximum mean scores for the variables range from 1 to 10. Higher scores indicate a greater endorsement of dysfunctional beliefs about sleep. A previous study demonstrated that the instrument has an acceptable test-retest reliability of 0.83 and an internal consistency of 0.79, indicating its suitability for measuring dysfunctional beliefs and attitudes about sleep [45].

#### Pre-Sleep Arousal Scale

Sleep arousal among medical students will be assessed using the Pre-Sleep Arousal Scale (PSAS), which consists of 8 items each for measuring somatic and cognitive arousal [46]. A 5-point Likert scale is used to present items depicting symptoms of arousal at bedtime [46,47]. Higher scores reflect higher presleep arousal. The minimum and maximum scores for both types of arousal range from 8 to 40. The instrument demonstrates internal consistency, with Cronbach α of 0.82 for the cognitive scale and 0.79 for the somatic scale [47].

#### Sleep Hygiene Index

The SHI is a 13-item self-report instrument used to assess behaviors that may compromise sleep hygiene [48]. Poor sleep hygiene has been significantly associated with poor SQ [49-51]. Scores range from 0 to 52, with higher scores indicating behaviors that compromise sleep. The scores can also be analyzed using percentile ranks, where scores below 26 indicate good sleep hygiene, scores between 27 and 34 represent normal sleep hygiene, and scores of 35 and above indicate poor sleep hygiene [48]. The SHI has an internal consistency reliability coefficient of 0.66 [48].

### Assessment of Participants’ Safety

The risk of severe or serious adverse events in this study is low, as no such events have been reported in previous studies using CBT-I for the management of insomnia [49].

Nevertheless, studies have shown that sleep restriction therapy, one of the components of CBT-I, may increase levels of vigilance impairment and daytime sleepiness among participants, potentially leading to adverse situations such as suicide attempts, incidents, and formal complaints about the online intervention [49]. As both the intervention and assessment will be conducted online, the researcher may not be made aware of all such events. The researcher will, however, instruct participants to complete a feedback form to report any self-reported adverse effects [50].

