Besides the overall recommendations on sleep hygiene, the medical students will be encouraged to focus on specific behaviors that received the highest scores in the Sleep Hygiene Index (SHI; ie, reducing coffee or alcohol consumption just before bedtime if the participant reports frequent use). They will also be guided by the Dysfunctional Beliefs and Attitudes About Sleep-16 (DBAS-16), particularly for participants who score highly on the item “feel irritable, depressed, or anxious during the day, mostly because I did not sleep well the night before.” This reflects a strong belief in the negative impacts of poor SQ. Such participants will be advised to explore whether there are any underlying reasons for their anxiety and depression, aside from insomnia.

The internet program will serve as the primary medium for delivering all intervention materials, with participants engaging with the materials independently. They will also have the opportunity to consult a clinical psychologist (see the “Withdrawal and Crisis Management Procedure” section). Additionally, participants are strongly encouraged to use the feedback form to contact a specialist, particularly if they are newly recruited into the RCT, experiencing negative effects from the ICBT-I or ISHE interventions, or encountering methodological or technical difficulties with the program. The content of the intervention is entirely based on the well-established ICBT-I, which has been validated and tested in previous studies [37].

Each module will be completed with a homework report, which participants will fill out and submit to their therapists. The therapist will review the report, worksheets, and sleep diary data. Written feedback will be provided within 48 hours, and the therapist will grant the medical student access to the subsequent module. Meanwhile, if the participant is inactive for 1 week, the therapist will be alerted via a mobile phone SMS text message, serving as a reminder and encouragement. If necessary, another SMS text message will be sent, followed by emails, with phone calls as the final step. The therapist (FM) in this study is a licensed clinical psychologist with expertise in poor SQ and insomnia-related CBT.

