### Withdrawal and Crisis Management Procedure

Participants can withdraw from the RCT at any time without penalty and are not required to provide reasons for their decision. In terms of crisis management, emergency psychiatric services will be available at UPM Teaching Hospital to assist participants in cases of crisis or distress that exacerbate their symptoms or lead to significant deterioration in functioning. All clinic attendees will have access to this service. The investigators will be notified if any medical student utilizes the emergency service, at which point a decision will be made regarding the RCT and whether the crisis qualifies as an adverse event related to the trial.

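### Apart from one notified emergency route, harms rest on participant-completed feedback forms, so harms counts by arm are open to under-reporting and differential reporting

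*Protocol article*

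**What the plan says.** In the protocol article, Assessment of Participants' Safety rates the risk of serious events as low. It then says that sleep restriction therapy "may increase levels of vigilance impairment and daytime sleepiness among participants". The same sentence goes on to name graver consequences, "potentially leading to adverse situations such as suicide attempts, incidents, and formal complaints about the online intervention". Because both treatment and assessment are online, it accepts that "the researcher may not be made aware of all such events". The response is that the researcher will "instruct participants to complete a feedback form to report any self-reported adverse effects".

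The intervention section (The Internet Group (CBT-I)) also mentions a feedback form. Participants are urged to use it to reach a specialist, for several purposes: being new to the trial, "experiencing negative effects from the ICBT-I or ISHE interventions", or having technical trouble.

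Withdrawal and Crisis Management Procedure gives a second route: "The investigators will be notified if any medical student utilizes the emergency service". They then decide whether the crisis counts as a trial-related adverse event. On location, the text says that "emergency psychiatric services will be available at UPM Teaching Hospital". No equivalent is named for UKM, the other recruiting university.

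**The concern.** The protocol identifies plausible harms, attaches them to one component of one arm, and admits that it may not hear of them. It then relies mainly on participants to report them. It attributes the gap to online conduct, yet online conduct is also what gives the trial a scheduled, reminded contact with every participant.

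Two things are at stake. Under-reporting lowers the counts in both arms, so a small number may reflect silence and not absence of harm. Differential reporting distorts the comparison between arms. Students are told their allocation and those in ICBT-I are the ones asked to restrict time in bed, so the readiness to report sleepiness or a near miss, or to attribute it to the programme, need not be equal.

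**Working it through.** The article states no harm rate, reporting rate or safety power, so there is no figure to reproduce. The check is a comparison of sections, followed by arithmetic on assumed rates.

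**Sections side by side**

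- Assessment of Participants' Safety: harms named, incompleteness admitted, feedback form relied on.
- The Internet-Based SHE: sleep restriction is not part of ISHE, so the named mechanism operates in one arm.
- Blinding: participants learn their allocation by automated email.
- Assessment Points and Outcome Measures (Overview): four post-baseline assessments (T1 to T4), sent by email, with reminders to those who have not finished within 2 days.
- Outcome Measures and Monitoring of Intervention and Follow-Up Assessment: the instruments are the PSQI, dTMT, DBAS-16, PSAS and SHI. None is described as asking about accidents or unwanted effects, and harms are not among the things reassessed at follow-up.
- Withdrawal and Crisis Management Procedure: emergency-service use is notified. This bears on acute crises, but would not pick up sleepiness or near misses.

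**Inputs for the arithmetic**

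- 60 per arm (Randomization and Allocation Concealment).
- 48 + 49 = 97 enrolled, all past T2 (Results). With a target of 120, at most 120 − 97 = 23 are still to come.
- Assumed, not in the article: true rate *p* and probability *s* that an event is reported.

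**Chance of at least one report in an arm of 60:** 1 − (1 − *p·s*)^60

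| True rate *p* | *s* = 100% | *s* = 50% | *s* = 25% |
|---|---|---|---|
| 1% | 0.45 | 0.26 | 0.14 |
| 2% | 0.70 | 0.45 | 0.26 |
| 5% | 0.95 | 0.78 | 0.53 |
| 10% | 1.00 | 0.95 | 0.78 |

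**Upper bound after zero reports in 60 (one-sided 95%):** 1 − 0.05^(1/60) = 0.0487 for the reported rate. Dividing by *s* gives the bound on the true rate: 4.9% at full reporting, 0.0487/0.5 = 9.7% at half, 0.0487/0.25 = 19.5% at a quarter.

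**Comparison of arms, equal reporting (two-sided 5%, normal approximation, 60 per arm):** true rates of 10% and 30% give power 0.79 with full reporting. At *s* = 50% the reported rates are 5% and 15% and power is 0.45. At *s* = 25% they are 2.5% and 7.5% and power is 0.24.

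**Comparison of arms, no true difference, unequal reporting:** with a true rate of 20% in both arms and reporting of 50% in one and 25% in the other, the reported rates are 10% and 5%. The chance of a nominally significant difference is then about 0.18, against the intended 0.05. With true rates of 10% and 30% it is 0.11 and 0.25.

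**The case against.** The strongest case on the other side has five parts.

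- **The form is not the only route.** Emergency-service use is notified to the investigators, which bears on suicide attempts, the gravest event named. Participants can consult a clinical psychologist, and the intervention section describes therapist review of each module and follow-up of inactive participants. The notified route stands as a genuine second source. The others are opportunities to hear of a problem, not described as asking about harms.
- **The form serves both arms.** A reader might infer that the trial cannot compare harms between arms or cannot detect the serious events it lists. The article does not support that. Counts from both arms will exist, and the table above shows that weaker reporting lowers detection without removing it.
- **Unequal therapist contact is not established.** A reader might infer that ICBT-I participants report more because a therapist sees them more often. The module review is described under the CBT-I heading, but Treatment Adherence refers to a therapist manual and supervision for both groups. The argument should rest on participants knowing their arm.
- **This is a condensed article.** The form's timing, its event list and the harms tabulation may be set out in a document not shown, so their absence is not the point here. What remains is the stated reliance on the form and the stated admission that events may be missed.
- **The reporting rates are invented.** They are assumptions, and even complete reporting leaves a 4.9% bound: with 60 per arm, rare serious events are hard to rule out however they are collected. This stands as a limit on the size of the point, not on its direction.

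**Conclusion.** The point holds in a limited form. The plan names harms tied to one arm, concedes incomplete knowledge of them, and relies on participant-completed forms plus one emergency route named at a single hospital, although it already has a scheduled contact with everyone. Harms counts by arm will therefore be open to under-reporting and, because participants are unblinded, to differential reporting. They can still be compared, but not relied on.

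The true size is unknown. Under assumed reporting of 25% to 100%, the zero-report bound for an arm of 60 ranges from 19.5% down to 4.9%. These figures fit best for harms that the emergency route would not pick up, such as accidents or near misses. The efficacy analyses are not affected. The point deserves correction because a better method is available within the existing assessments at little cost.

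**What to change.** - Add a short fixed set of harms questions to the existing online assessment, identical in both arms: daytime sleepiness, accidents or near misses, and any other unwanted effect.
- Ask them at every remaining assessment for students already enrolled, and at T1 to T4 for new recruits. For those already enrolled, the first such assessment should ask about the whole period since the intervention began.
- Tabulate answers by arm with the number asked as denominator. Keep the feedback form and the emergency-service notifications as additional sources, shown separately.
- Add a self-harm item only if answers can be handled through the crisis procedure the article already describes.
- State in the trial report that harms before the change were passively collected and that a low count is not evidence of safety.

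The cost is a few items per assessment and a notification to both ethics committees; no visit is added. The main limit is timing. Treatment and T2 are over for the 97 students enrolled, so their answers about the treatment period depend on recall, and at most 23 recruits could be asked from T1 onward. If T3 and T4 have also passed, only the reporting statement can still be made.
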